# Training secondary school students as anti-smoke ambassadors using the service-learning model: A cluster randomized controlled trial with hybrid type 1 effectiveness-implementation design study protocol

**DOI:** 10.1371/journal.pone.0313404

**Published:** 2024-11-14

## Abstract

**Background:**

Evidence shows that using the AWARD (Ask, Warn, Advise, Refer, Do-it-again) model with service-learning model in youngsters may be an appropriate strategy to refer young smokers for early smoking cessation services. Therefore this study aims to promote smoking cessation by training secondary school students as anti-smoke ambassadors (ASAs) with increased knowledge, skills and self-efficacy on smoking cessation and AWARD model using service-learning model.

**Methods:**

A cluster randomized controlled trial will be conducted in 14 secondary schools in Hong Kong. Also, a hybrid type 1 effectiveness-implementation design with the Reach Effectiveness Adoption Implementation Maintenance (RE-AIM) framework will be adopted. For the intervention group, participants (n = 184) will attend a 3-hour training workshop, followed by hands-on sessions supervised by trained nursing students, then a 6-month smoker referral competition and an award presentation ceremony. The control group (n = 184) will only attend the 3-hour training workshop. The research assistant will contact participants at the start and the end of training program, and at 3, 6, and 12 months after the end of the training program by telephone to complete a set of questionnaires. Participating secondary schools, participating nursing students, ASAs, and responsible organizational staff will be randomly invited for a one-to-one semi-structured interview. The primary outcome will be the number of smokers who referred by secondary school students. Descriptive statistics, mixed between-within-subjects ANOVA, logistic regressions, and content analysis will be used.

**Discussion:**

This study will bridge the gap in existing literature by determining the effectiveness and exploring facilitators and barriers in implementing our intervention with the use of the AWARD model and service-learning model in training young people to refer smokers to anti-smoke organizations in the real-world. This can enhance our community capacity and enable youngsters to take a proactive role to support smoking cessation.

**Trial registration:**

ClinicalTrials.gov, NCT05897346. Registered on 11 May 2023.

## Introduction

Smoking remains the leading cause of preventable premature death and illness worldwide [1], accounting for more than 8 million deaths annually [1, 2]. Evidence shows that smoking cessation interventions in young people are crucial for the tobacco endgame [3, 4], especially as smoking behavior from youth continues into adulthood [5]. Early smoking cessation interventions are pivotal.

Many young smokers who joined smoking cessation services were recruited through outreach activities and referrals from non-governmental organizations (NGOs) [6, 7]. Importantly, at the time joining the smoking cessation services, around half have already smoked for 4 years or more [6]. Given that early interventions are important for tobacco endgame [3, 4], more methods for recruitment has to be considered. Evidence shows that youngsters encounter peer smokers frequently and easily in their social network [5–8]. Building the community’s capacity by training youngsters to refer smokers to professional smoking cessation services therefore tend to offer a good strategy to support smoking cessation. Additionally, the trained youngsters will be educated about not smoking.

Studies also show that peer pressure is considered the most common reason for smoking in young people [5, 8]. Smoking cessation interventions that target peers are likely to have substantial effects. The second most common reason reported is curiosity [8]. This suggests that if young people clearly understand the consequences of smoking, they may be less likely to smoke because of curiosity. Evidence also indicates that youngsters may not have adequate knowledge about smoking and its consequences, which results in myths about smoking [9]. Once smoking behavior is initiated, individuals are easily addicted, which results in difficulty in quitting, thereby carrying smoking behavior into adulthood and later life [5]. Therefore, education to resolve these myths is particularly important.

Apart from resolving the myths in youngsters, a literature review revealed that brief interventions and referrals are important strategies to assist smokers to receive professional help to quit smoking successfully, as supported by the World Health Organization (WHO) and previous publications [10–12]. Particularly, the AWARD (Ask, Warn, Advise, Refer, Do-it-again) model emphasizes referrals and offers a brief and effective intervention for smoking cessation [11]. For instance, the Council on Smoking and Health and the Education Bureau in Hong Kong conducted the Smoke-free Elite Teens Program (formerly known as the Smoke-free Teens Program) [13, 14]. This program aims to nurture young people aged 14–18 years to promote a smoke-free culture in Hong Kong by firstly teaching participants the AWARD model and updated information on tobacco control, then requiring them to organize smoke-free programs in the community [13, 14]. The program has gained support from over 160 secondary schools, youth centers, and uniform groups. Nevertheless, the referrals rate was low with 1% of participants had referred smokers to smoking cessation services after the program [13]. One key possible reason is that the program did not provide hands-on experience to participants to proactively approach smokers and use the AWARD model. Some reported that they felt embarrassed and did not know how to effectively advise smokers to quit or refer smokers to professional services. Evidence also shows that hands-on experience is needed to effectively deliver learned skills [15].

In order to provide hands-on experience to youngsters, using service-learning model may be a suitable strategy [7, 16]. Service-learning models are used in some existing smoking cessation services such as Youth Quitline (YQL) [7]. YQL [7, 17] is a telephone hotline funded by the Department of Health in Hong Kong to train undergraduate nursing students to provides free peer smoking cessation counseling to young smokers aged 25 years or below. The quit rate in YQL is high [6], which represents a major success when compared with earlier results and other smoking cessation services in Hong Kong [6, 18]. YQL may be an appropriate venue for youngsters to gain hands-on experience of the AWARD model.

Hence our proposed study based on the service-learning model will provide opportunity for young people to learn and practice the AWARD model with hands-on experience under the supervision of nursing students who are considered peer counselors in YQL. However, no previous study has been conducted to explore the effectiveness, facilitators and barriers of our intervention in training young people to refer smokers to anti-smoke organizations in the real-world. Implementation study will be required to investigate facilitators and barriers of the interventions apart from the effectiveness, aiming to promote the systematic uptake of interventions in the real-world and hence improve the quality and effectiveness of health services [19].

### Theoretical models

#### AWARD model

The AWARD model involves an effective five-step process for smoking cessation when an individual encounters smokers: 1) Ask about smoking history, 2) Warn about the high risk of smoking, 3) Advise to quit; 4) Refer smokers to smoking cessation services; and 5) Do it again [11]. It emphasizes referral (i.e., referring smokers to existing smoking cessation services), which has been found to assist smokers to quit successfully [11]. This model is particularly suitable for young people as it is easily learned and used with minimal training [11]. Additionally, it takes only a minute or slightly longer to deliver smoking cessation advice based on the AWARD model [11]. Thus a large number of smokers can be reached at low cost [11].

Brief interventions using the AWARD model have been found to effectively assist smokers to quit and build community capacity for smoking cessation. Our previous study trained 50 girl guides to promote smoking cessation among community-living female smokers using the AWARD model which only lasted for a minute or slightly longer [11]. The findings showed that the intervention was feasible and effective in promoting smoking cessation among community-living female smokers [11].

#### Service-learning model

In this study, the service-learning model provides young people with opportunities to gain hands-on experience in using the AWARD model. The service-learning model has been used by universities over the past decade in teaching [20]. Service-learning is a type of experiential education that includes two fundamental constructs: service and learning [20]. The model requires senior or experienced workers who can monitor and supervise students in conducting activities when serving the community. It has been documented to benefit students by facilitating their intellectual and academic development and building their sense of civic responsibility through reflections and applying knowledge learned in classroom to real-world practice [20]. The model has also been published in our previous publication [7] and is currently being used to operate YQL. Under this model, nursing students are trained as peer counselors and receive supervision by nursing teachers while delivering smoking cessation counseling in their clinical placement in YQL.

### Aim and objectives

This study aims to promote smoking cessation by training young people as anti-smoke ambassadors (ASAs) with increased knowledge on smoking cessation and skills using the AWARD model to build community capacity in smoking cessation.

The objectives are to: 1) examine the effectiveness of our program in assisting secondary school students to refer smokers to YQL (primary objective), 2) increase ASAs’ knowledge about smoking cessation and skills using the AWARD model, 3) enhance their practice and attitudes toward smoking cessation and AWARD model, 4) increase their self-efficacy in using AWARD model skills, 5) provide hands-on experience in using the AWARD model through the service-learning model, 6) train ASAs to deliver brief interventions to young smokers using the AWARD model, and 7) identify facilitators and barriers in implementing in the real-world.

## Materials and methods

The recruitment of this study was started in 1 August 2023 and the tentative end date of the recruitment is 31 December 2024. The study protocol is consistent with the Standard Protocol Items: Recommendations for Intervention Trials (SPIRIT) (see S1 File). The schedule of enrolment, interventions, and assessments for SPIRIT is presented in Fig 1.

**Fig 1 pone.0313404.g001:**
[figure not shown]
Enrolment, intervention, and evaluation schedule for SPIRIT. The schedule of enrolment, interventions, and assessments for SPIRIT.

### Study design

A hybrid type 1 effectiveness-implementation design will be adopted as it can primarily focus on testing the effectiveness of our intervention on the relevant outcomes while observing and gathering information on implementation [21]. This can allow us to identify barriers, facilitators, and what is required for supporting the implementation in the real world and therefore inform the appropriate implementation strategies [21]. With the hybrid type 1 design, our main objective is to examine the effectiveness of the intervention. Information relating to implementation will also be studied as secondary outcomes. To do so, a two-arm cluster randomized controlled trial (RCT) following the CONSORT statement in Fig 2 will be conducted to examine the effectiveness of the program in referring smokers to YQL.

**Fig 2 pone.0313404.g002:**
[figure not shown]
CONSORT flow diagram. A recommended diagram to illustrate the flow of randomized controlled trials.

### Study setting

This is a 3-phased study conducted in 14 secondary schools in Hong Kong.

### Clusters and randomization

14 clusters (14 schools) will be randomized to the intervention or control group using a 1:1 ratio by a research assistant (RA) who is not from our team using an independent computerized randomization sequence process that can only be accessed by that RA to ensure allocation concealment. This RA will login to an online platform to perform randomization. Randomization sequences will be generated by the computer in randomly permuted blocks sizes of 2, 4, and 6. The RA responsible for recruitment will record the exact date and time of recruitment. Computerized time stamps and electronic logs of sent allocation will be used to ensure allocation concealment. The RA undertaking recruitment will be responsible for data collection and be blinded to the group assignment.

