**Fig 4 pone.0313404.g004:**
[figure not shown]
Checklist of the brief interventions using the AWARD model. The template of a checklist for ASAs to use in each intervention delivery.

Each ASA will be required to pass an examination before proceeding to the hands-on sessions. This examination has been adopted in our previous projects [6, 7, 11]. It will first involve a written test asking ASAs about their knowledge of smoking consequences and AWARD model, then an oral demonstration in response to a case scenario of a smoker (role-played by nursing students). The examinations will be assessed by our RA and team members, with 50% as the passing mark. Those who fail will be required to rejoin the training workshops and retake the examination until a passing mark is obtained.

*2*. *Hands-on sessions*. ASAs will then be required to follow their assigned nursing students to implement the brief interventions to smokers in Hong Kong. Specifically, nursing students will bring their ASAs to the outreach activities (2 hours each) to supervise ASAs delivering brief interventions using the AWARD model when encountering smokers aged 25 or below smoking. Each ASA will follow their respective nursing student to four outreach activities and two counseling sessions (2 hours each). During the counseling sessions, ASAs will listen to how the nursing students deliver smoking cessation counseling and join the conversations by applying the AWARD model, offering ASAs opportunity to experience smoking cessation counseling. All ASAs will receive a certificate after completion of this phase.

*3*. *Smoker referral competition*. All ASAs will then be given a 6-month period to use the AWARD model to deliver brief interventions to refer smokers who are aged 25 years or below to YQL independently, without the help of nursing students. To ensure ASAs’ safety, they are asked to approach smokers via their social network including peer smokers, smokers in families and schools. Smokers are defined as those who smoked tobacco products (including electronic cigarettes) in the previous 30 days, as defined in YQL and other projects related to smoking [6, 11].

Near the end of the brief intervention with the AWARD model, ASAs will provide the contact of YQL and invite the smokers to call YQL. Those who successfully contacted YQL staff will be regarded as a successful referral case.

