### Control group

Secondary school students will be only required to attend a 3-hour training workshops with AWARD model in their schools or the University by our trained RA. The contents of the workshops are the same as that in the intervention group. However control group will not join the examinations, hands-on sessions, the smoker referral competition nor be given checklists for conducting the brief interventions with AWARD model.

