### Data collection

After randomization, responsible teachers in schools will first be briefed by our RA about the purpose and protocol of the project. The schools will then distribute our promotional leaflets, information sheet and consent forms to students or parents depending on schools’ preferences. Consent forms with students’/parents’ telephone numbers will be returned to teachers if students are interested in joining the project. Eligible students will be informed by our RA via telephone that their participation will be voluntary and confidentiality will be maintained. They will also be notified about the details and schedule of the program activities.

The RA will contact the students in the intervention and control group at the start of training program (T1), at the end of training program (T2), and at 3 (T3), 6 (T4), and 12 months (T5) after the end of the training program by telephone to complete a set of questionnaires.

At T2, each ASA will submit a 300-word reflective journal. Responsible teachers in participating secondary schools, participating nursing students, ASAs, and responsible YQL staff will be randomly invited to complete a one-to-one semi-structured interview focused on implementation. The interviews will be conducted by an RA at T2 until data saturation is reached.

At T5, ASAs and nursing students will be interviewed about maintenance. Another RA who is not involved in this project will be asked to generate random numbers using a computer for random selection of participants for the interviews. All interviews will last for around 15–30 minutes and be audio-recorded in a room in our university or online (e.g., via Zoom) depending on the preference of interviewees. Based on the interview guide developed by our team, they will be asked about their overall experience, facilitating factors, barriers, and feasibility of implementing brief interventions using the AWARD model to smokers at T2. At T5, they will be asked about the maintained effects and components of the project. It is estimated that around 40 and 20 interviewees will be needed to reach data saturation at T2 and T5, respectively. Each interviewee will receive HKD$200 as a travelling allowance.

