### Limitations of the study

One limitation is that blinding is not possible in this study. Second, this study can only provide follow-ups up to 12 months. Longer follow-ups may help explore the long-term impact of our intervention on participants in the real-world setting. Third, attritions will be expected. However, our sample size estimation has increased the sample size to a potential loss to follow-up up to 10%. Finally, the finding of this study is only applicable in smoking cessation but not in other addictive behaviors. However, it is expected that future studies may use our finding as the foundation to explore the possibility in implementing in other addictive behaviors.

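### The research assistant who recruits and collects data is called blinded, but recruitment as described follows school randomisation and reveals the arm, so blinded data collection is not delivered for the telephone self-reports

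*Protocol article*

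**What the plan says.** Three parts of the protocol article bear on whether the data collector is blinded.

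- **Clusters and randomization** gives recruitment and data collection to one RA and calls that RA blinded: "The RA undertaking recruitment will be responsible for data collection and be blinded to the group assignment".
- **Data collection** sets the order of events. "After randomization, responsible teachers in schools will first be briefed by our RA about the purpose and protocol of the project". Schools then distribute leaflets and consent forms. "Eligible students will be informed by our RA via telephone that their participation will be voluntary and confidentiality will be maintained", and the next sentence adds: "They will also be notified about the details and schedule of the program activities". The RA telephones both arms for questionnaires at five time points, T1 to T5.
- **Limitations of the study** says: "One limitation is that blinding is not possible in this study". It does not say whose blinding is meant.

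Two further places matter. **Control group** sets out what that arm does not receive: "However control group will not join the examinations, hands-on sessions, the smoker referral competition nor be given checklists". The description of the smoker referral competition, in **Phase 2: Training program**, defines the event behind the primary outcome: "Those who successfully contacted YQL staff will be regarded as a successful referral case".

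**The concern.** A person who recruits students in a school already allocated, and who passes on or discusses what those students will be doing, learns that school's arm. If the same person then makes the questionnaire calls, the interviewer is not blinded, whatever the randomisation section says.

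The outcomes at stake are those that students report about themselves by telephone. Under Measurements these are practice and attitudes (31 items, including how often the student delivered the brief intervention and to how many smokers) and self-efficacy (3 items scored 1 to 10). They serve objectives 3 and 4 at T1 to T5, and count again as maintenance outcomes at T5. An interviewer who knows the arm can prompt, probe or code differently without meaning to. A trial report that repeated the randomisation section would also claim a safeguard that the described procedure does not provide.

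**Working it through.** The point involves no arithmetic beyond adding sessions. The check is whether the described steps allow the data collector to remain blinded.

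1. **Who collects the data.** Clusters and randomization: the recruiting RA. To recruit is therefore to be the later interviewer.
2. **When recruitment happens.** Data collection: after randomisation of schools. The arm is fixed before the first contact with teachers or students.
3. **What passes in recruitment.** Data collection: an RA explains the purpose and protocol to teachers and telephones eligible students, and students are told the content and timetable of the activities.
4. **Whether that content identifies the arm.** Phase 2 and Control group, side by side:
   - Both arms: the same 3-hour workshop.
   - Intervention only: an examination, 4 outreach activities + 2 counselling sessions = 6 supervised sessions of 2 hours each (6 × 2 = 12 hours), checklists, a 6-month referral competition and an award ceremony.
   - Control only: nothing further.

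   A schedule with one workshop cannot be confused with a schedule that also has six sessions and a competition. Anyone who conveys either one knows the arm.
5. **How far one disclosure reaches.** Allocation is by school, and the sample size section expects 28 students per school. One student's remark about an outreach session can therefore reveal the arm of about 28 students.
6. **Other routes to the same knowledge.** Under Measurements, an unspecified RA logs examination passes, outreach sessions and competition entrants, all of which exist only in the intervention arm. T2 falls at the end of training, which comes after the hands-on sessions in the intervention arm. If T2 in control schools is dated from the workshop, the timing of the call may itself point to the arm; the article does not say how it is dated there.
7. **Which outcomes depend on the interviewer.**
   - Practice, attitudes and self-efficacy: self-report in RA telephone calls, so exposed.
   - Knowledge: 19 fixed statements answered true, false or don't know, which leave little room for interviewer influence.
   - Referrals (primary, at T4): defined by the smoker reaching YQL staff, an event outside the questionnaire call. The article does not say who counts referrals or attributes them to students.

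Steps 1 to 4 lead to an interviewer who knows the arm, provided the RA in step 3 is the recruiting RA of step 1. The Limitations sentence agrees with that result and does not exempt the assessor.

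**The case against.** The strongest reply is that the article never says the RA who telephones students is the recruiting RA of the randomisation section. Data collection refers only to the team's RA, and the sentence on the schedule is in the passive. Several RAs appear in the article: one outside the team who randomises, a workshop trainer, an examiner, an interviewer, and another who draws the interview sample. An article may leave the division of roles to the full protocol. This stands as a limit: the identity is an inference. It is a close one, since briefing schools and calling prospective participants is recruitment, and the article names the recruiting RA as the data collector.

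Second, the Limitations sentence may mean only that participants and providers cannot be blinded, which would be compatible with a blinded assessor. That reading is fair. A reader might infer that the randomisation and Limitations sections flatly contradict each other, but the documents support only that the Limitations sentence is unqualified and needs its scope stated. The firmer conflict is between the randomisation section and the recruitment procedure.

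Third, a reader might infer that all outcome assessment, including the primary outcome, is unblinded. The documents do not support this. Nothing says that referrals are taken from the telephone questionnaire, and their definition points to YQL contact.

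Fourth, social-desirability bias comes largely from students who know their own programme. This also stands: blinding the interviewer would remove only the interviewer's contribution. Nor do the two programmes differ throughout, since the workshop content is the same in both; it is the additions that reveal the arm.

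**Conclusion.** The point holds in limited form. The procedure described does not deliver the blinding claimed for the person who recruits and collects data, and the Limitations section does not say whose blinding it rules out. The consequence falls mainly on practice, attitudes and self-efficacy at T1 to T5. Knowledge is less exposed. The primary outcome is less exposed too, though the article leaves open who counts referrals.

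The size of any bias cannot be derived from the article. The conclusion rests on one assumption: that the RA who briefs schools and telephones students is the recruiting RA. If another person does this and the data collector is kept away from allocation, the claim could be true, but the article would need to say so. The sample size is not affected. This should be corrected, but it does not undermine the primary comparison.

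**What to change.** 1. Have someone other than the data-collecting RA, for example the workshop RA or the responsible teacher, brief schools and convey the schedule to students.
2. Withhold allocation, and the logs of intervention-only activities, from the data-collecting RA.
3. Use one identical call script in both arms, opening with a request not to mention programme activities.
4. State that referrals are counted from YQL records, in line with the article's own definition of a successful referral.
5. Reword Clusters and randomization and Limitations of the study to say that participants and providers are unblinded, and which assessor is blinded for which outcomes.
6. If the roles cannot be separated, delete the blinding claim and report the self-reported outcomes as collected by an unblinded interviewer.

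The cost is the reassignment of the recruitment contacts and a short script. It should need no new staff if the RAs already mentioned can absorb the contacts, which is an assumption about staffing. Some accidental unblinding will remain, and students' own knowledge of their programme will still colour their answers.

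Recruitment was tentatively open until 31 December 2024 and follow-up runs to 12 months after training, so the separation could still protect later calls if they are made by someone who did not recruit. For calls already made, the report should say who made them and what that person knew. The wording can be corrected at any time.
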